## Abstract

**Background:**

Myopia is a public health problem worldwide and its incidence increases with age. The use of acupuncture to treat myopia is a common practice in China, however, the use of acupuncture to treat myopia is disputed in other parts of the world. This study aims to determine the safety of acupuncture to treat myopia and its efficacy over six months.

**Methods/Design:**

A randomized, parallel, single-center, assessor- and statistician-blinded, controlled clinical trial will be performed. A total of 100 teenagers, between seven and 12 years of age, with mild-to-moderate myopia and spherical lenses <-6.00 D and cylindrical lenses <-1.50 D will be selected from the Xinjiang Uygur Autonomous Region Institute of Traditional Chinese Medicine, a grade III level A teaching hospital in Urumqi, Xinjiang, China (Xinjiang Medical University Affiliated Hospital of Traditional Medicine). The subjects will be randomly assigned to two different groups (control and acupuncture groups), each group containing 50 subjects. The subjects in both groups wear single-vision corrective lenses. In the acupuncture group, acupuncture will be performed daily for nine consecutive days on five points (bilateral Cuanzhu, Tongziliao, Sibai, Muchuang, and Hegu), followed by no treatment for one day. Six cycles of treatment will be undertaken continuously for a total of 60 days. Following 60 days of treatment, a follow-up period of six months will be included. The primary outcome will be diopter determination. The secondary outcomes will include distance visual acuity, axial length, lens thickness, ciliary body thickness, and subjective symptoms of the eyes and entire body. The main time points for the evaluation of clinical efficacy will be the first, third, and sixth months after treatment.

**Discussion:**

This study will provide clinical observations of various indices following the use of acupuncture to treat adolescents with mild-to-moderate myopia, as well as information on the safety of acupuncture.

**Trial registration:**

Chinese Clinical Trial Registry (identifier: ChiCTR-TRC-13003448; registration date: 7 August 2013).

## Background

Myopia is becoming increasingly common and has become a worldwide public health issue
[1]. In the United States and Europe, the incidence of myopia is 20% to 50%
[2]; in Asian countries, such as mainland China, Taiwan, Hong Kong, and Singapore, the incidence of myopia is 60 to 80%
[3–5]. Over the past 50 to 60 years, the incidence of myopia in East and Southeast Asian countries has rapidly increased. Approximately 80 to 90% of urban adolescents in these countries have myopia on graduating from high school
[1]. Myopia often occurs between six and eight years of age, develops rapidly between 13 and 16 years of age, and stabilizes after 16 years of age
[6]. Treatment of myopia in modern medicine is mainly optometric, and includes the use of spectacles (single-vision lenses (SVLs) and progressive addition lenses
[7] and contact lenses
[8, 9]. Refractive surgeries include laser-assisted *in situ* keratectomy, photorefractive keratectomy
[10–12], and posterior chamber phakic intraocular lenses
[13]. However, while the most commonly used treatment method (optometric) can increase the best corrected visual acuity, optometric methods are unable to improve the uncorrected visual acuity. Surgery can help eliminate the need for glasses, but may lead to complications, as indicated by long-term follow-up studies
[13, 14]. There is also an age limit for performing such surgery, and it is considered as the last treatment choice for teenagers.

Acupuncture is highly valued in traditional Chinese medicine, and enjoys a favorable history of more than 2,500 years. Acupuncture has helped millions of patients around the world, and has been shown to be effective in clinical treatment. In 1980, the World Health Organization recommended acupuncture as an effective alternative therapy
[15]. Previous studies have confirmed that acupuncture, ear pins, or ear massage can help treat mild myopia (<-3.0 D)
[16]. There are published reports on the use of acupuncture in the treatment of adolescent myopia, but most studies use visual acuity as the primary outcome measure. Indeed, visual acuity, as determined by eye examination, is easily influenced by many external factors. Therefore, we have designed a randomized controlled trial based on the physiology and pathology of myopia. In addition to using distance visual acuity, diopter, and axial length (AL)
[17] as indices of clinical observation, indices such as ciliary body thickness
[18] and lens thickness
[19] will also be utilized to obtain more objective and quantitative results. This trial aims to confirm the effectiveness and safety of acupuncture in the treatment of adolescent myopia.

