### Study design

This study will be a randomized, parallel, single-center, assessor- and statistician-blinded, controlled trial. The included subjects will be assigned to groups in a 1:1 ratio. The subjects (n = 100) will be randomly assigned to experimental (n = 50) and control groups (n = 50). The experiments began in January 2013 and will be completed in December 2014. The aim of this study is to objectively evaluate the clinical efficacy of acupuncture at five acupuncture points (bilateral Cuanzhu, Tongziliao, Sibai, Muchuang, and Hegu) in adolescent teenagers with mild-to-moderate myopia (Table 
1, Figure 
1). This report will be compiled according to the SPIRIT (Standard Protocol Items: Recommendations for Interventional Trials) 2013 Statement ‘*Defining Standard Protocol Items for Clinical Trials*’
[20].

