### Statistical analysis

All statistical analyses will be performed using SPSS 17.0 statistics software. For quantitative data, the distribution pattern and homogeneity of variance will be examined. If there is a symmetric distribution, the mean (M) ± standard deviation will be used for statistical description, otherwise the M interquartile range (IQR) will be used to describe the trend of concentration and amount of scatter. If this condition is met, the Student's t-test will be used to compare the differences between the quantitative indices between the groups, otherwise the Wilcoxon rank-sum test will be used. For categorical data (binary classification and multiple classification), the composition ratio will be used for statistical description. Based on the observation of a theoretical frequency distribution, the χ^2^ or Fisher's exact test will be used, depending on the specific situation. The ranked data will be analyzed using the Wilcoxon rank-sum test.

Primary and secondary outcomes will be analyzed by the superiority test in accordance with the principle of intention-to-treat, using Per Protocol Set (PPS) and Full Analysis Set (FAS) datasets. The indices of safety evaluation will be analyzed using the Save Set (SS) dataset. The significance level in this study will be set at α = 0.05, and the one-sided test will be used. The detailed statistical analytical methods for primary and secondary outcomes and baseline data are shown in Table 
2 (variables, measures, and methods of analysis).

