**Table 2 Tab2:** **Variables, measures, and methods of analysis**

Variable/outcome	Hypothesis	Outcome measure	Methods of analysis
1) Primary	Intervention improved outcome from baseline to 7 days	Adherence% (>80%) [binary]	
Diopter	Diopter reduced or increased after treatment	Diopter [continuous]	t-test (rank-sum test) or repeated measurement
2) Secondary	Intervention improved outcome from baseline to 7 days	Adherence% (>80%) [binary]	
Visual acuity	Visual acuity did not increase or decrease after treatment	Visual acuity changes [continuous]	t-test (rank-sum test) or repeated measurement
Axial length	Axial length was not increased	Axial length changes [continuous]	t-test (rank-sum test) or repeated measurement
Lens thickness	Lens thickness was not increased	Lens thickness changes [continuous]	t-test (rank-sum test) or repeated measurement
Ciliary body thickness	Ciliary body thickness was not increased	Ciliary body thickness changes [continuous]	t-test (rank-sum test) or repeated measurement
Eye symptoms and systemic symptoms	No adverse symptoms	No adverse symptoms	Chi-squared test or Fisher’s exact test
Compliance	Compliance	Cure rate [binary]	Chi-squared test or Fisher’s exact test
Combination therapy/treatment	Improvement occurred	Whether other drugs were used during treatment [binary]	Chi-squared test or Fisher’s exact test
Adverse event	Improvement occurred	Presence of drug-related adverse event [binary]	Chi-squared test or Fisher’s exact test
3) Baseline analyses:		Adherence% (>80%) [continuous]	
Age		CRF [continuous]	t-test (rank-sum test)
Weight and height		CRF [continuous]	t-test (rank-sum test)
Female versus male		CRF [binary]	Chi-squared test or Fisher’s exact test
Race		CRF [more categories]	Chi-squared test or rank-sum test
Birth weight		CRF [continuous]	t-test (rank-sum test)
Preterm children		CRF [binary]	Chi-squared test or Fisher’s exact test
Parental myopia or not		CRF [binary]	Chi-squared test or Fisher’s exact test
Sibling myopia or not		CRF [binary]	Chi-squared test or Fisher’s exact test
Daily close reading time		CRF [continuous]	t-test (rank-sum test)
Outdoor time		CRF [continuous]	t-test (rank-sum test)
Eye exercises every day or not		CRF [binary]	Chi-squared test or Fisher’s exact test
Daily sleep time		CRF [continuous]	t-test (rank-sum test)
Room light conditions		CRF [binary]	Chi-squared test or Fisher’s exact test
Poor reading habits		CRF [more categories]	Chi-squared test or rank-sum test

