The limitations of the proposed study are three-fold. Firstly, due to a limited budget, the proposed study will not be a multicenter trial, which will influence the external validity of the conclusions. Secondly, common fake acupuncture methods include neighboring sham acupuncture, non-specific site acupuncture, superficial acupuncture, minimal acupuncture, and a placebo needle; all of these methods could be used as a control, but with obvious deficiencies
[33]. Therefore, in the proposed study a sham acupuncture group will not be included. Quantitative, objective indices, such as diopter, AL, lens thickness, and ciliary body thickness will be selected as the outcomes to evaluate the clinical efficacy at a reduced bias. Thirdly, in the proposed study, 100 cases will be included and followed up on for six months. To prevent bias caused by loss-to-follow-up, the following measures will be adopted: first, the subjects will be from an elementary school near the hospital. Second, before the subjects are entered into the proposed study, their guardians will fully understood the specific requirements of the follow-up schedule, as outlined in the informed consent form. Once the subjects are included in the study, communication with the guardians will be strengthened by phone calls or email. The subjects will be informed of the follow-up examination time and place in advance. The subjects will receive the follow-up examination immediately after arriving.

This will be a randomized, parallel controlled trial, and it is anticipated that acupuncture treatment of adolescent mild-to-moderate myopia will be shown to be safe and effective. The proposed study will demonstrate the specificity of the meridians and acupuncture points and provide evidence-based medical evidence on the use of acupuncture to treat myopia.

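### The trial sets out to confirm safety, but its only inferential adverse-event analysis is a between-arm difference test with no margin, and a non-significant result there cannot support a safety conclusion

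*Protocol article*

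**What the plan says.** The article words its safety aim in several ways.

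- Abstract, Background: "This study aims to determine the safety of acupuncture to treat myopia and its efficacy over six months".
- Background, closing sentence: "This trial aims to confirm the effectiveness and safety of acupuncture in the treatment of adolescent myopia".
- Discussion, closing paragraph: "it is anticipated that acupuncture treatment of adolescent mild-to-moderate myopia will be shown to be safe and effective".

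On analysis, the adverse-event row of Table 2 reads across its columns (variable, hypothesis, measure, method) as "Adverse event Improvement occurred Presence of drug-related adverse event [binary] Chi-squared test or Fisher’s exact test". Eye and systemic symptoms get the same pair of tests in their own row. The Statistical analysis section chooses between the two tests with the phrase "Based on the observation of a theoretical frequency distribution", that is, by expected counts. It names the safety population: "The indices of safety evaluation will be analyzed using the Save Set (SS) dataset". It sets alpha at 0.05 with one-sided testing and describes categorical data by proportions.

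On size, Study design states: "The subjects (n = 100) will be randomly assigned to experimental (n = 50) and control groups (n = 50". The Sample size section works from diopter alone. No acceptable harm rate, safety margin, reference event rate or precision target for safety appears.

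The Harms section names bleeding, hematoma, fainting, severe pain and local infection. Controls wear single-vision lenses and receive no needling (Intervention section).

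**The concern.** The aim and the method do not fit together. A difference test takes equal event rates as its null hypothesis, so failing to reject says little when the arms are small. To support a claim of safety, the plan needs either a rate that would count as acceptable or an estimate with an upper limit, and the article offers neither.

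The comparison is also a weak tool for part of the list. A control child who is never needled should not have needle bleeding or a needle hematoma, so for those events the informative quantity is the incidence in the acupuncture arm.

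The hypothesis printed in the adverse-event row, that improvement took place, has no clear meaning for an adverse event. If the one-sided direction followed it, the test would not look for harm at all.

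The participants are children aged 7 to 12, with most needle points on the face or head, and the authors already expect a favorable safety result. A safety claim beyond what the data can bear would matter.

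**Working it through.** **Plan's own figure.** There is none for safety, so nothing can be reproduced on this point. The sample size rests on diopter.

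**Inputs.** 50 children per arm (Study design). One binary outcome per child, "Presence of drug-related adverse event [binary", read here as related to the study treatment (Table 2). Alpha 0.05 one-sided (Statistical analysis); the two-sided result is also shown because the Sample size section says two-sided. The denominator is 50 exposed children: the Excluded cases section keeps excluded children with at least one session in the adverse-reaction analysis, and the Dropout cases section keeps dropout data for analysis.

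**Assumption.** The control rate for needle bleeding and hematoma is 0%. The article gives no rate, so other values are shown below.

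**Step 1: which observed counts pass.** With x events in 50 acupuncture children and none in 50 controls, one-sided Fisher p = C(50,x)/C(100,x). With equal arms the two-sided p is twice that.

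- x = 4: 230,300/3,921,225 = 0.059 one-sided, 0.117 two-sided.
- x = 5: 2,118,760/75,287,520 = 0.028 one-sided, 0.056 two-sided.
- x = 6: 15,890,700/1,192,052,400 = 0.013 one-sided, 0.027 two-sided.

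The largest count that passes is therefore 4/50 (8%) one-sided and 5/50 (10%) two-sided.

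**Step 2: chance of a significant result in the direction of harm.** With no control events this is P(X ≥ 5) one-sided and P(X ≥ 6) two-sided, X ~ Bin(50, true rate). With control events, all pairs of counts are enumerated.

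| True rate, acupuncture v control | One-sided | Two-sided |
|---|---|---|
| 5% v 0% | 0.104 | 0.038 |
| 8% v 0% | 0.371 | 0.208 |
| 10% v 0% | 0.569 | 0.384 |
| 15% v 0% | 0.888 | 0.781 |
| 12% v 2% | 0.463 | 0.313 |
| 15% v 5% | 0.388 | 0.244 |

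A true 10% v 0% is missed 1 − 0.569 = 43% of the time one-sided and 1 − 0.384 = 62% two-sided. Any background rate makes this worse for the same ten-point excess. A power of 80% needs a true rate of about 13% (one-sided) or 15% (two-sided).

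**Step 3: does the choice of test matter?** An uncorrected chi-squared test would detect 10% v 0% with probability 0.888 one-sided and 0.750 two-sided. But 5 v 0 events gives expected event counts of 2.5 per arm, where Fisher's test would normally be used.

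**Step 4: what estimation gives instead.**

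- Zero events in 50: exact two-sided 95% upper limit 1 − 0.025^(1/50) = 7.1%, about 1 in 14.
- 4/50, non-significant one-sided: exact 95% interval 2.2% to 19.2%.
- At a true 10% rate, the chance of at least one event is 1 − 0.9^50 = 99%.

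The arm is large enough to show that such harm exists. It is the test that may fail to flag it.

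**The case against.** The strongest reply is that the article nowhere says a p-value above 0.05 will be read as proof of safety. That stands. A reader might infer such a rule from a confirmatory aim paired with a difference test, but it remains an inference. Four other stronger readings also go too far.

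- **That only a test is planned.** The Statistical analysis section already describes categorical data by proportions, and the Harms section says adverse events will be reported. What is absent is an inferential basis that suits the claim.
- **That harm seen in one child in ten would pass.** Under the one-sided rule, 5/50 v 0/50 is significant if the test looks for harm (p = 0.028). Only the two-sided label in the Sample size section lets it pass.
- **That the safety denominator falls to 40 after 20% dropout.** The sections on dropout and excluded cases keep these children's data, so 50 is the proper figure, assuming each receives at least one session.
- **That the control rate is zero by design for every listed event.** Fainting, severe pain, local infection and general symptoms can occur in controls, and a between-arm comparison informs on those.

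The wording is also uneven. The Abstract's Discussion promises only information on safety, the Study design aim mentions efficacy alone, and the Discussion sentence is an expectation rather than a decision rule. Exact intervals and event listings are details that an article may leave to a fuller document.

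These points narrow the criticism but do not remove it. The article itself fixes the aim, the endpoint, the hypothesis and the test, and those four do not agree.

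**Conclusion.** The point holds as a mismatch between a confirmatory safety aim and a difference test that cannot deliver it. Under the article's one-sided rule, a true needling-harm rate of 10% would go unflagged 43% of the time; two-sided, 62%. These figures assume 50 children analyzed per arm, Fisher's test, a one-sided test directed at harm, and no such events in controls. The number of exposed children is not itself the fault: 50 can support an estimate with an upper limit, but not a conclusion that the treatment is safe. The documents do not show that the sponsor intends to equate non-significance with safety. They do leave that path open, and the hypothesis in the Table 2 row is wrong for an adverse event on any reading.

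**What to change.** 1. Base the safety conclusion on the per-child incidence of each event named in the Harms section, in the acupuncture arm of the safety set, with exact 95% confidence intervals. List serious events individually.
2. Keep the between-arm comparison as supportive only, for events that can also arise in controls: fainting, pain, infection and symptoms.
3. Correct the hypothesis in the adverse-event row of Table 2.
4. In the Background and the closing Discussion, replace the language of confirming or showing safety with estimating the incidence of adverse events, and align the Abstract's aim with it.
5. State that observing no events in 50 children cannot exclude a rate below about 1 in 14.

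Per-session rates are optional and make sense only if the case record form dates events by session, which the article does not show.

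The cost is a change of wording and of the planned safety summary, with no change to treatment, visits or sample size. The downside is a more modest safety claim.

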## Methods/Design

### Ethics and dissemination

This trial was designed and will be implemented in accordance with the relevant provision on the protection of rights and interests of the subjects in the Declaration of Helsinki version 08 and the ‘*Biological Ethics Review Method Involving Humans*’ by the Ministry of Health of the People's Republic of China (2007). The implementation of this project has been reviewed and approved by the Ethics Review Committee of Xinjiang Medical University Affiliated Hospital of Traditional Chinese Medicine. The Certificate number of the ethics review is 2013 XE008-1. Written informed consent will be obtained from the guardians of each of the participants.

### Study design

This study will be a randomized, parallel, single-center, assessor- and statistician-blinded, controlled trial. The included subjects will be assigned to groups in a 1:1 ratio. The subjects (n = 100) will be randomly assigned to experimental (n = 50) and control groups (n = 50). The experiments began in January 2013 and will be completed in December 2014. The aim of this study is to objectively evaluate the clinical efficacy of acupuncture at five acupuncture points (bilateral Cuanzhu, Tongziliao, Sibai, Muchuang, and Hegu) in adolescent teenagers with mild-to-moderate myopia (Table 
1, Figure 
1). This report will be compiled according to the SPIRIT (Standard Protocol Items: Recommendations for Interventional Trials) 2013 Statement ‘*Defining Standard Protocol Items for Clinical Trials*’
[20].

**Table 1 Tab1:** **Time of visit and data collection**

Data obtained/recorded	Baseline	Treatment phase	Visit 1	Visit 2	Visit 3
	-7 days	1-2 months	3 months	5 months	8 months
Signed informed consent	×				
Medical history	×				
Met the diagnostic standard/exclusion criteria	×				
General record	×				
Diagnosis	×				
Visual acuity	×		×	×	×
Diopter	×		×	×	×
Axial length	×		×	×	×
Lens thickness	×		×	×	×
Ciliary body thickness	×		×	×	×
Skin damage	×	×	×	×	×
Eye symptoms and systemic symptoms	×	×	×	×	×
Randomization	×				
Group therapy	×				
Case report form	×		×	×	×
Adverse event		×	×	×	×
Close-out					×

**Figure 1 Fig1:**
[figure not shown]
**Flow of participants.**

### Recruitment

This study will be conducted in the Department of Ophthalmology, Xinjiang Uygur Autonomous Region Institute of Traditional Chinese Medicine (Xinjiang Medical University Affiliated Hospital of Traditional Chinese Medicine, a grade III level A teaching hospital). Adolescents with mild-to-moderate myopia will be recruited from the 27th Elementary School near the Xinjiang Uygur Autonomous Region Institute of Traditional Chinese Medicine after an ophthalmologic examination. Inclusion criteria will be as follows: the result of retinoscopy is myopic refractive error; distance visual acuity can be corrected to normal using negative spherical or cylindrical lenses; near visual acuity and other visual functions must be normal; myopia diopter spherical lenses must be between -0.5 D and -6.00 D, and cylindrical lenses <1.5 D, as measured under cycloplegia; and adolescents must be between seven and 12 years of age. Exclusion criteria will be as follows: subjects with serious systemic diseases, such as cerebrovascular, liver, kidney, hematopoietic system, and psychiatric diseases; long-term use of other related drugs or treatments, which have not been terminated; diopter < -0.5 D, or combined with pathologic myopia-related fundus changes and/or significant visual function impairment; and the affected eyes have other diseases which affect the determination of acupuncture efficacy.

